### Population Sampling

Purposive sampling will be conducted to ensure quotas for different demographics are captured. Individuals are eligible to enroll in the study if they: (1) are aged 18 to 30 years; (2) reside in NSW; (3) own or have access to a smartphone; (4) can read, write, and understand English; and (5) consume at least one meal, snack, or drink purchased outside the home per week. As the data will be collected using a smartphone app in English, it is important that the participants have access to a smartphone and are proficient in written English. The study is specifically focused on foods eaten away from home, so it is important that participants eat out at least once per week. Participants will be excluded if they do not meet the aforementioned criteria, are not able to commit to 3 consecutive days of data collection, are pregnant and/or breastfeeding, or have ever been diagnosed or treated for an eating disorder. Pregnant women and breastfeeding mothers will be excluded as their nutritional requirements, and potentially eating habits, change during this time. Those who have been diagnosed or treated for an eating disorder will be excluded because of ethical reasons.

A total of 1008 participants will be recruited to the study, across a range of geographic areas and demographic factors, which provides a margin of error of ±3% on all estimates of proportions (with 95% CI). An even spread of males and females will be recruited. The sample will be constituted to ensure an even distribution of participants in the older age bracket (25 to 30 years) and the younger age bracket (18 to 24 years); from metropolitan and regional areas (as defined by the Accessibility/Remoteness Index of Australia (ARIA+) [29] based on the postcode of the area the participant resides, with major cities considered “metropolitan” and all other areas “regional”); and from lower and higher SES areas (as defined by the Index of Relative Socio-economic Advantage and Disadvantage (IRSAD) [30] based on the postcode of the area where the participant resides) with “low” SES, including deciles 1-5 and “high” SES deciles 6-10). The sampling diagram is shown in Multimedia Appendix 1.

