Data will be collected on 3 consecutive days, and across the entire sample the start days will be spread to capture data for an equal number of weekdays and weekends. In total, data will be collected for 3024 days, including 1512 weekdays (considered Monday to Thursday) and 1512 weekends (Friday to Sunday) to allow for differences between weekdays and weekends to be investigated. Fridays were considered weekend days as previous research has shown that eating habits on Fridays are more like Saturdays and Sundays than weekdays [42].

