### Statistical Analysis

#### Mean Intake of Energy and Nutrients

Data collected from the EaT app will be used to determine mean, median, and 95% CI of daily intakes of energy, macronutrients, and micronutrients as well as the contribution of each of the macronutrient to energy content. Misreporting of energy intake will be identified using the Goldberg criteria [50], and sensitivity analysis will be undertaken to assess their inclusion or exclusion from the primary analysis. Energy and nutrient intakes will be compared with Australian Nutrient Reference Values [51] applicable for each age and sex group and the usual intakes from the latest Australian Health Survey [6]. Multivariate regression models will be used to determine the various health, social, and environmental factors associated with consumption of energy and nutrients. To control for multiple comparisons, a significance level of *P*<.01 will be considered for these calculations.

Demographics questionnaire.Anthropometry and diet statusSelf-reported height and weightHow often the participant attempted weight loss in past 12 months, including currentlyWhether the participant is motivated by eating healthy food, losing weight, staying fit and active, or their appearanceDiet and eating behaviorsSelf-perceived healthiness of their dietFood avoidance for health, cultural, or ethical reasons, including vegetarianismSupplement useFrequency and usual timing of meals and snacksFood securityAdequacy of factors influencing diet, including cooking skills, cooking equipment, time available to cook, and access to healthy foods in their local areaQuality and variety of healthy foods in their local areaWho does the cooking in their householdHow often meals and snacks are eaten in front of the televisionAverage weekly amount they spend on eating out of homeReasons for eating out of homeNutrition literacyKnowledge of the Australian Government’s recommended number of serves of the 5 core food groupsHealth behaviorsAlcohol consumption and consumption patternsPhysical activity and sedentary behaviors at work and during leisure timeSleep patterns and durationSelf-perceived health and well-beingTobacco and e-cigarette useDietary monitoringWhether they would be interested in logging single foods with appsWhat aspects of their diet would participants be interested in logging (if any)Eat and Track app usabilityEase of useIf the app is frustrating to useWhether the participant had to make corrections

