#### Consumption of Foods Purchased and Eaten Away From Home

The average frequency of meals, drinks, and snacks (collectively, and by occasion) purchased and eaten away from home will be calculated. Multivariate regression models will be used to determine the health, social, and environmental factors associated with consumption of foods purchased and eaten away from home. The relative contribution of foods purchased and eaten away from home to total energy and macronutrient intake will be calculated.

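### Half of the recorded days are Friday–Sunday, which make up 3/7 of the week, and no day weighting is stated for the whole-week averages

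*Protocol article*

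**What the plan says.** In Methods, under The Eat and Track Dietary Intake App, the article states: "Data will be collected on 3 consecutive days". Across the sample, "the start days will be spread to capture data for an equal number of weekdays and weekends". The resulting total of 3024 days is described as "including 1512 weekdays (considered Monday to Thursday) and 1512 weekends (Friday to Sunday".

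The reason given is "to allow for differences between weekdays and weekends to be investigated". Friday is grouped with the weekend because earlier research found that "eating habits on Fridays are more like Saturdays and Sundays than weekdays".

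Under Statistical Analysis, the subsection on mean energy and nutrient intake plans as follows: "Data collected from the EaT app will be used to determine mean, median, and 95% CI of daily intakes of energy", with macronutrients and micronutrients treated the same way. For eating out, the later subsection of the analysis says: "The average frequency of meals, drinks, and snacks (collectively, and by occasion) purchased and eaten away from home will be calculated". That subsection also plans the share of energy and macronutrients that comes from these foods.

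No section mentions weighting or standardising by day of the week, and none says that the averages will be unweighted.

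**The concern.** The day allocation and the headline estimates serve different purposes. An equal split is efficient for comparing the two day types. An average day or week needs them in the proportion 4 to 3. The article fixes the first and does not connect it to the second.

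This matters because the article treats the day types as potentially different: it plans to investigate the difference, and it classifies Friday by how people eat on that day. The quantities affected are the study's main results, namely how often young adults eat out, how much they consume per day, and what share of intake comes from food bought away from home. A plain average of the collected days describes a week with 3.5 weekend days. More participants would narrow the interval around that figure but would not move it.

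A related, smaller issue arises at person level. Three consecutive days can hold different numbers of Friday–Sunday days depending on the start day, so a participant's own average partly reflects when recording began.

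**Working it through.** **Inputs from the article**
- Participants: 1008 (Population Sampling: "A total of 1008 participants will be recruited to the study").
- Days per participant: 3, consecutive.
- Weekend: Friday–Sunday, 3 of 7 days. Weekday: Monday–Thursday, 4 of 7.
- Weekend–weekday difference in intake or eating out: not given, so assumed below.

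**1. The plan's own figure.** 1008 × 3 = 3024 and 3024 / 2 = 1512. It reproduces exactly.

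**2. Calendar-proportional split.** 3024 × 3/7 = 1296 Friday–Sunday days and 3024 × 4/7 = 1728 Monday–Thursday days. The plan therefore holds 1512 − 1296 = 216 more weekend days: 50.0% against 42.9%, or 7.1 percentage points.

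**3. Start days.** Friday–Sunday days in a 3-day window, by start day:

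| Mon | Tue | Wed | Thu | Fri | Sat | Sun |
|---|---|---|---|---|---|---|
| 0 | 0 | 1 | 2 | 3 | 2 | 1 |

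Starts spread evenly over all seven days give 9/21 = 3/7, so the 50/50 target needs an uneven choice of start days. One such choice is equal use of Wednesday, Thursday, Saturday and Sunday: (1 + 2 + 2 + 1)/12 = 1/2, with both day types in every participant.

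**4. Bias of a plain mean.** Let D be the Friday–Sunday mean minus the Monday–Thursday mean. The plain mean differs from the whole-week mean by (1/2 − 3/7) × D = D/14. Averaging person means gives the same result, because each participant contributes three days.

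As a relative bias, with r the weekend:weekday ratio: [(1 + r)/2] / [(4 + 3r)/7] − 1.

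| Assumed r | Plain mean | Whole-week mean | Relative bias |
|---|---|---|---|
| 1.0 | 1.000 | 1.000 | 0 |
| 1.1 | 1.050 | 1.043 | +0.7% |
| 1.2 | 1.100 | 1.086 | +1.3% |
| 1.5 | 1.250 | 1.214 | +2.9% |
| 2.0 | 1.500 | 1.429 | +5.0% |

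Means are in units of the weekday mean. A ratio below 1 reverses the sign. In absolute terms, assumed energy differences of 200, 500, 1000 and 1500 kJ/day give 14, 36, 71 and 107 kJ/day.

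**5. Cost of weighting.** Weights are calendar share over sample share: (4/7)/(1/2) = 8/7 for Monday–Thursday and (3/7)/(1/2) = 6/7 for Friday–Sunday. The Kish design effect is [0.5 × (8/7)² + 0.5 × (6/7)²] / 1² = 100/98 = 1.020, or about 3024/1.020 ≈ 2964 effective days. Intervals widen by √1.020 ≈ 1.01, about 1%. This ignores correlation between a participant's three days.

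**The case against.** The strongest objection is that the article nowhere says the averages are unweighted. A weighted mean is still a mean, and a condensed article may leave the weights to an analysis plan that is not shown. The equal split is also deliberate, explained and a valid stratified allocation. Both points stand. A reader might infer that the design is faulty or that the plan commits to unweighted averaging; the article supports neither. What remains is that it fixes a disproportionate allocation for one comparison and then describes the main estimates in terms that, followed as written, carry the disproportion into them.

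It is also tempting to conclude that eating out will be overstated. The article gives no direction, and the positive figures above follow from choosing ratios above 1.

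A reader might say that the results cannot be compared with the national survey. That survey's distribution of days is not in the article, so this cannot be judged.

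On person-level outcomes, a reader might infer that some participants must record no weekend days and others only weekend days. The article does not say which start days are used, and step 3 shows a 50/50 schedule in which everyone has both types. Varying day mix is a feature of any three-consecutive-day design; it is not caused by the equal split. Spreading starts evenly over the week would not cure it, since that schedule includes windows with 0 and with 3 weekend days. If start dates are unrelated to participant characteristics, linear regressions would mainly gain noise rather than bias.

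**Conclusion.** The point holds in a limited form. The article gives Friday–Sunday half of the recorded days against 3/7 of the week and states no day weighting for whole-week intakes, eating-out frequency or intake shares. If plain averages are used, the error in a mean is 1/14 of the weekend–weekday difference: zero with no difference, and +0.7% to +5.0% for assumed ratios of 1.1 to 2.0. This rests on three assumptions: that the averages are plain, that the 1512/1512 target is met, and that the ratio lies in the assumed range. The likely bias is modest. It falls on the study's headline estimates, however, does not diminish with sample size, and costs almost nothing to remove, so the change is worth making.

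**What to change.** Keep the 1512/1512 collection and use it for the weekday–weekend contrast. Add a sentence to the Statistical Analysis section stating that whole-week means, frequencies and energy or nutrient shares weight Monday–Thursday days to 4/7 and Friday–Sunday days to 3/7. With the planned split the day weights are 8/7 and 6/7; if the achieved split differs, compute them as calendar share over achieved share. Confidence intervals should allow for the three days coming from one person.

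In person-level regressions, adjust for the number of Friday–Sunday days recorded. Do not use that count as a clustering input, because it would pull the clusters toward start day. Do not claim that day weights repair whether a participant meets the recommended serves when only one day type was recorded; the other type is unobserved for that person.

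The cost is one weight variable, one covariate and about 1% wider intervals for the weighted estimates, before within-person correlation. Data collection does not change.

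### Friday to Sunday makes up half of the recorded days but 3/7 of the week, and the overall daily means, eating-out frequencies and away-from-home shares are described without day weights

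*Protocol article*

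**What the plan says.** Population Sampling sets the sample size: "A total of 1008 participants will be recruited to the study". The Eat and Track Dietary Intake App section sets the recording scheme. Each person keeps a record for three days in a row, and the rule for allotting start days is this: "across the entire sample the start days will be spread to capture data for an equal number of weekdays and weekends". The section gives the overall count ("In total, data will be collected for 3024 days") and then the split between day types ("including 1512 weekdays (considered Monday to Thursday) and 1512 weekends (Friday to Sunday"). The stated reason for the split is "to allow for differences between weekdays and weekends to be investigated". Friday is grouped with the weekend because earlier research found Friday eating closer to Saturday and Sunday than to the other days.

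Under Statistical Analysis, Mean Intake of Energy and Nutrients plans the "mean, median, and 95% CI of daily intakes of energy, macronutrients, and micronutrients", to be compared with Australian reference values and with usual intakes from the national survey. Mean Consumption of Food Groups plans mean intakes and the proportion of participants who meet recommended serves. Consumption of Foods Purchased and Eaten Away From Home says: "The average frequency of meals, drinks, and snacks (collectively, and by occasion) purchased and eaten away from home will be calculated". It adds the relative contribution of these foods to energy and macronutrients. None of these subsections mentions day-of-week weights, standardisation to a seven-day week or a usual-intake model. None uses the word unweighted either.

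**The concern.** The allocation of days is disproportionate by design: Friday to Sunday is oversampled relative to the calendar. That suits a comparison of the two day types. It does not suit an average meant to describe a typical day or week unless the oversampling is undone in the analysis. The article's own reason for grouping Friday with the weekend implies that eating differs by day type, which is the condition under which the imbalance matters.

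The affected quantities are central ones: average daily intake, how often young adults eat out, and what share of their intake comes from food bought away from home. Averaging within participants first does not help. Each participant contributes three days, so the mean of the participant means equals the mean over all days. The shift is systematic, so a larger sample would narrow the interval around the shifted value without moving it.

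**Working it through.** **Inputs from the protocol article.** 1008 participants (Population Sampling); 3 days each, split 1512 and 1512 (The Eat and Track Dietary Intake App).

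**The plan's own figure.** 1008 x 3 = 3024, and 3024 / 2 = 1512. Both reproduce exactly.

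**Calendar share.** Friday to Sunday is 3/7 = 42.9% of a week. Of 3024 days that is 1296, leaving 1728 for Monday to Thursday. The plan has 1512 - 1296 = 216 more Friday-Sunday days than that, an excess of 50.0% - 42.9% = 7.1 percentage points.

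**An even spread of start days would not produce this.** Three consecutive days starting on Monday, Tuesday, ... Sunday contain 0, 0, 1, 2, 3, 2, 1 Friday-Sunday days. That is 9 of 21 = 3/7. With 1008 / 7 = 144 starts on each day, 144 x 9 = 1296. The 50:50 split therefore needs a deliberate tilt of start days.

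**Shift in a plain mean.** Let A be the Monday-Thursday mean and B the Friday-Sunday mean.

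- Plain average: A/2 + B/2
- Calendar average: 4A/7 + 3B/7
- Difference: (1/2 - 3/7)(B - A) = (B - A)/14

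**Size on a percentage scale** (assumed gaps B - A, since the article gives none):

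| Gap (points) | Shift (points) |
|---|---|
| 5 | 0.36 |
| 10 | 0.71 |
| 20 | 1.43 |
| 30 | 2.14 |

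For example, shares of 30% and 45% give 37.5% plain and 4/7 x 30 + 3/7 x 45 = 36.4% weighted.

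**Size as a ratio** (assumed R = B/A). Relative shift = [(1 + R)/2] / [(4 + 3R)/7] - 1. R = 1.1, 1.2 and 1.5 give 0.7%, 1.3% and 2.9%. If R is below 1 the shift is downward; if R = 1 there is none.

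**Pooled energy share.** Here the 1/14 is exact only if total energy is equal on the two day types. If Friday-Sunday energy were 1.2 times weekday energy (assumed), the Friday-Sunday share would carry weight 1.2/2.2 = 0.545 instead of 3.6/7.6 = 0.474. The difference is 0.072, close to 1/14 = 0.071.

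**Scale.** The stated margin of ±3% for proportions corresponds to 1.96 x sqrt(0.25/1008) = 3.09%. A shift of 3 points would need a gap of 3 x 14 = 42 points.

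**Cost of weighting.** Day weights are (4/7)/0.5 = 8/7 = 1.143 and (3/7)/0.5 = 6/7 = 0.857. Day-level design effect = (1.143² + 0.857²)/2 = 1.02. This treats days as independent with equal variance, so it is approximate.

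**The case against.** The strongest objection is that this argues from silence. The article is a condensed account, the analysis plan is not shown, and the weights could be specified there. Nothing in data collection prevents it: the split is planned and every entry is date-stamped. It stands that the article never commits to unweighted estimates; that is inferred from the plain averages it describes. It does not dispose of the point, because the article itself fixes a disproportionate allocation and then states overall estimates from it. If the full plan already has the weights, one sentence settles the matter.

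A second objection is that oversampling a stratum for a planned contrast is ordinary practice. That is right, and the split is not an error.

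A third is that the effect is small and its inputs are assumed. That also stands.

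Three stronger readings are tempting and are not supported:

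- **That eating out will be overstated, perhaps substantially.** The article implies that the day types differ but gives no direction or size for any outcome.
- **That the comparison with national usual intakes is biased by a known amount.** The article does not describe that survey's coverage of days.
- **That the same day weights repair every outcome.** A participant with no Friday-Sunday day, or with three, has only one day type, so the 4/7 and 3/7 combination cannot be formed for that person. The proportion meeting recommended serves is a person-level outcome and is not corrected this way. Medians of participant averages have the same difficulty, and the 1/14 formula does not apply to them.

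**Conclusion.** The point holds in a limited form. Computed as plain averages, overall mean intakes and eating-out frequencies are shifted by 1/14 of the Friday-Sunday minus Monday-Thursday difference, and pooled away-from-home shares by close to that. Sign and size are unknown from the article. Assumed gaps of 10 to 20 points give 0.7 to 1.4 points, below the stated ±3% margin but not reduced by recruiting more people. An outcome that does not differ by day type is unaffected.

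This rests on three assumptions: that the achieved split matches the planned one, that the estimates are meant to represent an ordinary week, and that no weighting is specified elsewhere. It merits a stated correction in the analysis. It gives no reason to change data collection.

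**What to change.** State in the Statistical Analysis section that overall population mean intakes, eating-out frequencies and pooled away-from-home shares are computed as 4/7 x Monday-Thursday plus 3/7 x Friday-Sunday. This is equivalent to day weights of 8/7 and 6/7 under the planned split; if the achieved split differs, the weights should be recalculated from the achieved counts. For pooled shares, weight the numerator and denominator before dividing. Cluster standard errors by participant, since each contributes three days. Keep the unweighted split for the weekday-weekend contrast only.

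Do not apply these day weights to the proportion of participants meeting recommended serves. Use an adjustment for each participant's mix of day types, or a usual-intake model, and say which.

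For means, frequencies and shares the cost is one added sentence and about 2% of effective sample size, with no change to recruitment or recording. The person-level outcome takes more work, because it needs a model rather than a reweighting.

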### Data Cleaning

All app entries will be checked by study investigators in the 2 days following data entry, to allow time for data to be returned from the app server. Participants will be contacted to clarify any freeform text entry food items and inconsistencies such as gross data entry errors and skipped meals. When a recipe is entered by the participant without the quantities of ingredients, the recipe database from AUSNUT 2011-2013 will be used to identify and quantify the individual recipe ingredients and assign the appropriate food codes. If no recipe exists in this database, popular recipe websites Taste Australia and international equivalents will be used.

### Demographic and Usability Questionnaire

Once participants complete the 3 consecutive days of data collection, they will complete the final, extensive demographics questionnaire (Textbox 3). Of the 43 demographic questions included in this questionnaire, 31 (72%) have been previously validated or used in other epidemiological surveys [22,43-45]. The questionnaire will collect self-reported height and weight data, as well as questions on self-perceived health status, and health behaviors such as physical activity and sedentary behavior levels, smoking status, alcohol consumption, stress levels, sleep patterns, and self-rated well-being. Specifically on diet and weight, there will be questions on perceived healthiness of their diet; food avoidance for health, ethical, or religious reasons; frequency of dieting to lose weight, whether participants are trying to lose or gain weight, and how much they care about their weight and appearance. The number of daily meals and snacks and the usual timing of these will be assessed and compared with entries from the app. The self-reported frequency and amount spent on foods purchased and eaten away from home will also be collected over the 3-day study period. Additionally, there will be questions on social factors, such as who they live with, who does the cooking in their household (if anyone), perceived ability to access and cook healthy foods, barriers to accessing and cooking healthy foods, and food security. Participants will be asked about the Australian Dietary Guidelines’ [46] recommended number of serves for each of the five food groups to assess their nutrition literacy. Finally, participants will evaluate their perceived usability of the EaT app in the final questionnaire by answering the 4 questions of the Usability Metric for User Experience [47].

